### Objectives of this study

The objective of this study is to investigate the effects of a multifaceted intervention, existing of medication review and a CBT intervention for medication adherence, on the occurrence of DRP in elderly patients of 60 year and older discharged from the hospital using five or more drugs. The hypothesis of this study is that this multifaceted intervention will reduce the occurrence of DRP and improve compliance. The secondary objectives are to evaluate the effect of the intervention on: attitude to drugs, incidence of Re-hospitalisations related to medicines, functional status of the patient, quality of life. Moreover, the cost-effectiveness of this intervention will be analysed.

## Methods/Design

### Design of the study

The study is designed as a randomized, controlled, intervention study involving 342 patients with a follow-up of one year. The intervention will be performed by community pharmacists. A flow-chart of the study is shown in Figure 2.

**Figure 2 F2:**
[figure not shown]
**Study Design**.

The Medical Ethics Committee of the VU University medical enter in Amsterdam approved the study design, protocols, information letters and informed consent form.

### Setting

The trial will be conducted in 23 community pharmacists in Amsterdam, Amstelveen, Hoofddorp and Diemen, the Netherlands. The medication review will be performed by a pharmacist in close collaboration with the general practitioner (GP). The patients will be counseled at home or in the pharmacy by a pharmacy technician.

### Study Population

A total of 342 patients discharged from any department, except oncology and psychiatry, from any general and academic hospital in Amsterdam, Amstelveen, Hoofddorp and Diemen will be enrolled into the study. Patients 60 years and older, using five or more prescription-only chronic drugs when admitted to the hospital are considered eligible to participate into the study. The pharmacists will evaluate whether the patient uses 5 or more chronic drugs. Furthermore, to participate, the patients have to give written informed consent.

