**Methods/Design:**

A randomized controlled trial will be performed. Community pharmacists will be randomized into a control group and an intervention group. 342 Patients, aged over 60 years, discharged from general and academic hospitals, using five or more prescription drugs for their chronic disease will be asked by their pharmacy to participate in the study.

Patients randomized to the control group will receive usual care according to the Dutch Pharmacy Standard. The medication of patients randomised to the intervention group will be reviewed by the community pharmacist with use of the national guidelines for the treatment of diseases, when patients are discharged from the hospital. The Pharmaceutical Care network Europe Registration form will be used to record drug related problems. Trained pharmacy technicians will counsel patients at home at baseline and at 1,3,6,9 and 12 months, using Cognitive Behaviour Treatment according to the Theory of Planned Behaviour. The patient's attitude towards medication and patient's adherence will be subject of the cognitive behaviour treatment. The counselling methods that will be used are *motivational interviewing *and *problem solving treatment*. Patients adherence towards drug use will be determined with use of the Medication Adherence Report Scale Questionnaire. There will be a follow-up of 12 months.

The two primary outcome measures are the difference in occurrence of DRPs between intervention and control group and adherence with drug use. Secondary endpoints are attitude towards drug use, incidence of Re-hospitalisations related to medicines, functional status of the patient, quality of life and the cost-effectiveness of this intervention.

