### Treatment allocation

Ten Pharmacotherapeutic Audit Meetings (PTAMs) will participate in the study. In the Netherlands general practitioners and pharmacists are organized in PTAMs. Within a PTAM pharmacists are randomized as a control or intervention pharmacist.

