##### Cognitive behaviour treatment

Patients randomised to the intervention group will also receive cognitive behaviour treatment (CBT) at baseline and 1, 3, 6, 9 and 12 months by a pharmacy technician, with help of a structured interview protocol and with use of communication and motivational interviewing skills at home or in the pharmacy. The first session will be within one week of inclusion in order not to delay participant program admission. During these sessions the result of the medication review will be discussed with the patient. The patient will be informed about the effects, side effects and use of the drugs. Patients will be counselled according to the motivational interviewing principle to sustain or improve their drug adherence. The patients understanding of his or hers condition and its treatment are considered when appropriate. If possible, home supplies of drugs are checked and rationalised at each visit. All patients receive a written outline of their drug regimen. Cancelled and redundant drugs are taken in. During the session, over the counter remedies will be included in the medication review. All sessions are done by pharmacist technicians with help of a structured protocol. The patient visit will take 30-60 minutes.

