#### Control Group

Patients of control pharmacists will receive usual care according to the Dutch Pharmacy Standard (Table 1). Furthermore, patients are visited once by a pharmacy technician and asked about possible drug related problems. These problems will be registered for scientific use only.

**Table 1 T1:** Usual care, according to the Dutch Pharmacy Standard

1	Preceding the release check, prescriptions are routinely checked for drug interactions and contra-indications by the PAIS.
2	Discharge medication is delivered at the patients' home or is picked up by the patient or carer in the pharmacy.
3	Drugs are routinely delivered with a drug information leaflet but patients often are also handed supplementary personalized PAIS-generated information letters on newly prescribed drugs.
4	When the discharge medication is collected from the pharmacy, the patient or carer is also provided with additional oral information about newly prescribed drugs. This includes an explanation of the drugs' actions, their use and of possible side effects.

First edition of 1996. The current (2nd) edition was introduced in 2006 (KNMP, The Hague).

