### Analyses

Descriptive statistics (means ± SD or median and interquartile range in case of a skewed distribution) will be used to describe the whole study sample with regard to demographics, drug use and reason for previous hospital admission. The analyses will be conducted according to the intention-to-treat principle. To assess the impact of the intervention, multilevel linear and logistic regression analyses will be conducted to study differences in outcome measures between patients of the intervention and control pharmacies. Using multilevel analyses enables taking clustering of observations of participants receiving care from the same GP and for repeated measurements within one subject in account. Differences in changes between groups are measured with 95% confidence intervals. We will adjust data for possible confounders and effect modifiers (age, sex, ethnicity, level of education). Separate analyses of effect modifiers and mediators will be conducted in order to gain a better understanding which subgroups benefit most from the intervention. Confidence intervals of differences in costs between groups will be estimated using bootstrapping methods. (Bootstrapping statistics is a general method for performing statistical analyses without making strong parametric assumptions [32].

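### Pharmacies that know their arm judge eligibility and invite patients after allocation, while the stated covariates omit number of drugs, so case mix may differ and be only partly corrected

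*Protocol article*

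**What the plan says.** **Allocation.** The Treatment allocation section states: "Within a PTAM pharmacists are randomized as a control or intervention pharmacist". The abstract and the section on cognitive behaviour treatment also speak of randomised patients, but the only allocation procedure described is at pharmacist level.

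**Recruitment.** Under the abstract's Methods/Design, patients "will be asked by their pharmacy to participate in the study". Under Study Population, "The pharmacists will evaluate whether the patient uses 5 or more chronic drugs".

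**Timing and burden.** In the intervention arm, "The first session will be within one week of inclusion", with further sessions at 1, 3, 6, 9 and 12 months, each visit lasting 30 to 60 minutes. In the control arm, "patients are visited once by a pharmacy technician".

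**Entry criterion.** Study Population counts patients "using five or more prescription-only chronic drugs when admitted to the hospital". The Objectives section refers to patients "discharged from the hospital using five or more drugs", and the abstract's Discussion also ties the count to discharge.

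**Analysis.** The Analyses section says: "We will adjust data for possible confounders and effect modifiers (age, sex, ethnicity, level of education". Drug use and reason for admission appear there only among the variables that describe the sample. The same section plans multilevel models with repeated measurements and between-arm differences in change. The Outcome Measures section has DRPs determined at baseline and at 12 months by independent clinical pharmacologists.

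**The concern.** When clusters are randomised first and patients recruited afterwards by staff who know the arm, randomisation balances the pharmacies but not the patients who enter through them. An intervention pharmacist might, without intending to, invite patients with more problems or with problems that look easier to solve. A control pharmacist has no such prompt. The interventions also ask very different amounts of patients' time, so willingness to take part may differ between arms.

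The first mechanism bears on the DRP comparison, in an unknown direction. The second bears on self-reported adherence, the other primary outcome. The four adjustment variables are demographic and say little about the drug regimen, which is what a pharmacist sees when deciding whom to invite. The limitations in the Discussion cover differences between pharmacists and technicians in skill and time, but not recruitment after allocation.

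**Working it through.** **1. Is the recruiter aware of the arm?** No single sentence says so, and the flow chart is not shown. The order is inferred:
- Allocation is of pharmacists (Treatment allocation).
- Only intervention pharmacists attend the medication review course, and only intervention technicians the counselling courses (training sections).
- The first session falls within one week of inclusion, so a pharmacy must be allocated and trained before it includes patients.
- The pharmacy itself invites patients and judges the drug count.

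No recruiter blind to arm and no listing of patients before allocation is described.

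**2. Does the covariate list cover what can be selected on?** The Background names number of drugs, number of diagnoses and number of prescribers as risk factors. None is among age, sex, ethnicity and education. The pharmacy's dispensing record holds the drugs dispensed to each patient, so a drug count can be extracted in both arms.

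**3. What does the change analysis remove?** Take no treatment effect and write the contrast as (control change) − (intervention change). The percentages below are assumed, except the 30% control level from the Sample size section.
- Stable gap: control 30% to 30%, intervention 25% to 25%. Contrast = 0 − 0 = 0. The bias cancels.
- Problems that resolve more readily: control 30% to 30%, intervention 30% to 25%. Contrast = 0 − (−5) = 5 points. It does not cancel.
- Regression to the mean: control 30% to 30%, intervention 35% to 30%. Contrast = 0 − (−5) = 5 points. It does not cancel.

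Medicine-related re-hospitalisation is counted during follow-up with no baseline value described, so no change contrast exists for it.

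**4. Illustration of scale.** The plan gives no figure for this bias. Its total of 342 patients at a ratio of one gives 342/2 = 171 per arm. (On the stated inputs, 30% v 20%, two-sided 0.05 and 80% power, the unpooled formula gives (0.21 + 0.16) × (1.960 + 0.842)² / 0.10² = 290.4 per arm, and 290.4/0.85 = 341.7. So 342 resembles a per-arm number. That is a separate matter; here 342 is the total, as the article states.)

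For a 12-month comparison of two proportions without baseline or covariates, no treatment effect and an assumed selection difference d from 30%:

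rejection = Φ[(d − 1.96·SE0)/SE1] + Φ[(−d − 1.96·SE0)/SE1]

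SE0 = √(2·p̄(1−p̄)/n) is pooled, SE1 = √([p1(1−p1) + p2(1−p2)]/n) is unpooled, and n = 171.

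For d = 0.05: SE0 = √(2 × 0.275 × 0.725/171) = 0.0483 and SE1 = √((0.2100 + 0.1875)/171) = 0.0482. Then Φ(−0.93) + Φ(−3.00) = 0.177 + 0.001, about 0.18.

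| Assumed difference | n = 171 per arm | n = 171 × 0.85 = 145 per arm |
|---|---|---|
| 2 points | 7% | 7% |
| 5 points | 18% | 16% |
| 8 points | 39% | 34% |
| 10 points | 57% | 50% |

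The last column applies the article's 15% allowance for clustering. The planned 30% to 20% effect is 10 points, so a 5-point difference is half of it.

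**The case against.** The strongest reply is that the plan already measures DRPs at baseline with independent assessors and analyses differences in change. That stands in part: a stable difference in level largely cancels. It leaves the other items in step 3 and the re-hospitalisation outcome open.

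Age and a count from dispensing records are also fairly objective. This stands too, and moves the main room for selection to whom the pharmacy invites, what counts as chronic, and who consents.

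A condensed article may also leave a longer covariate list to a fuller document. If such a list contains the drug count, that part of the point is already met. The article, however, does name a list.

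Some stronger readings are tempting but unsupported:
- **That the trial's false positive rate is 18%.** This figure follows from an assumed 5-point shift in an unadjusted 12-month test, which is not the planned analysis.
- **That the room for selection is large.** Spreading 342 patients over January 2008 to March 2009 (15 months) and 20 to 23 pharmacies gives 342/(20 × 15) = 1.14 to 342/(23 × 15) = 0.99 per pharmacy-month, or 25% to 29% of the 4 forecast. On the six months of actual recruitment in the Sample size section, the share is 342/(4 × 6 × 20) = 342/480 = 71%. Pharmacies may have started at different times, the forecast may have been too high, and the article does not say whether 342 was reached.
- **That patients consented knowing their arm's burden.** The information letters are not shown.
- **That the arms counted drugs at different dates.** The same text governs both arms. The admission and discharge wordings conflict, but nothing shows that they were applied differently by arm.

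**Conclusion.** The point holds as a risk of differential case mix, not as evidence that it occurred. It rests on the inferred order of allocation and inclusion, which the text supports well. The baseline DRP measurement and change analysis give real but partial protection. The size and direction of any remaining bias cannot be derived from the article, and the 7% to 57% range only shows how an uncorrected comparison would respond to assumed shifts. The clearest weakness that can still be repaired is that the stated covariates leave out number of drugs, which the article itself treats as a risk factor. Adjustment would reduce the bias but not remove it, and a drug count does not capture motivation, the main threat to the adherence outcome.

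**What to change.** The article reports that inclusion has been performed, so the remedy lies in analysis and reporting.

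1. Add the baseline number of chronic drugs to the covariates of the primary multilevel models and of the re-hospitalisation model. Count it from pharmacy records at one fixed date, in the same way in both arms, and before the medication review, because the review may change the regimen. Add reason for admission in a few broad categories if the model supports it.
2. Include the baseline value of each outcome where it was measured.
3. Compare baseline characteristics by arm. Report the numbers eligible from pharmacy records and the numbers included, by arm, where these can be retrieved. Numbers invited need an invitation log, which the article does not describe.
4. Name recruitment after allocation by unmasked pharmacies as a limitation, and say that covariates reduce this bias without removing it and do not measure motivation.
5. Reconcile the admission and discharge wordings of the five-drug criterion.

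The cost is one or two model terms, a modest extraction from pharmacy systems, and a few sentences of text. The article lists drug use as a descriptive variable but does not say that a count at a given date was recorded, so some extraction time should be expected.

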### Treatment allocation

Ten Pharmacotherapeutic Audit Meetings (PTAMs) will participate in the study. In the Netherlands general practitioners and pharmacists are organized in PTAMs. Within a PTAM pharmacists are randomized as a control or intervention pharmacist.

### Study procedures

#### Intervention group

##### Medication review

The medication of patients in the intervention group will be reviewed by the community pharmacist using the full record of prescription only drugs which were dispensed by the patients' pharmacy and the patients medication evaluation profile. This profile shows when the patients has obtained his medication from the pharmacy. The GP will be consulted by telephone for details about indications for drugs and results from laboratory tests. When prescribed by a medical specialist, details about the indication for the drug will be obtained from the specialist, who will be consulted by the community pharmacist. The National guidelines for treatment of diseases will be used by community pharmacists as a method for performing medication review.

The Pharmaceutical care network Europe DRP-score form will be used to record drug problems. Each drug will be evaluated on adverse reactions, drug choice problems, dosing problems, drug use problems, drug-interactions or other problems. Causes for drug related problems will be assessed and interventions will be made. During the medication review the patient will be involved as a full partner. Any changes made will be communicated with the patient. This method for medication review will be pilot tested before use.

The occurrence of drug related problems will be discussed with the GP. The result may be an adaptation of the drug regimen. The medication review will take 10-30 minutes per patient and will depend on the complexity of the medication regimen and problems detected.

##### Cognitive behaviour treatment

Patients randomised to the intervention group will also receive cognitive behaviour treatment (CBT) at baseline and 1, 3, 6, 9 and 12 months by a pharmacy technician, with help of a structured interview protocol and with use of communication and motivational interviewing skills at home or in the pharmacy. The first session will be within one week of inclusion in order not to delay participant program admission. During these sessions the result of the medication review will be discussed with the patient. The patient will be informed about the effects, side effects and use of the drugs. Patients will be counselled according to the motivational interviewing principle to sustain or improve their drug adherence. The patients understanding of his or hers condition and its treatment are considered when appropriate. If possible, home supplies of drugs are checked and rationalised at each visit. All patients receive a written outline of their drug regimen. Cancelled and redundant drugs are taken in. During the session, over the counter remedies will be included in the medication review. All sessions are done by pharmacist technicians with help of a structured protocol. The patient visit will take 30-60 minutes.

##### Training course pharmacists

All participating intervention pharmacists will participate in a one day medication review training course. During this training session the background of medication review will be explained. The use of Medication Evaluation Profiles will be explained. Furthermore, the way the PCNE DRP-score form should be used will be explained.

To pilot test the interrater variability of the PCNE DRP-score form and the efficacy of the medication review training all participating pharmacists (controls and intervention pharmacists) will receive 5 medication overviews of test-patients with additional information about clinical notes approximately three months before the medication review training session. The results of the medication reviews will be evaluated by a specialist in medication review.

When intervention pharmacists have completed the training course in medication review, all pharmacists (control and interventions) will be asked to review five new test-patients. The intervention pharmacists are expected to detect more DRPs afterwards than control pharmacists who did not receive a special training in medication review. The results of the medication reviews will be evaluated by the same specialist as before.

##### Training pharmacy technicians

All intervention technicians will participate in a two days training course of motivational interviewing and a one day course of problem solving treatment. During these training sessions pharmacy technicians will be lectured about communication skills such as Motivational interviewing and Problem solving treatment skills by a specialized psychologist on this subject. In addition pharmacy technicians will receive coaching on the job. Video tapes of interviews with patients will then be recorded and reviewed by two independent researchers using the Motivational Interviewing Treatment Integrity Code score method to evaluate the quality of the motivational interviewing skills of the pharmacy technicians.

##### Pharmacotherapeutic Audit Meetings (PTAM)

In addition, to improve the intervention and its performance, the intervention will be discussed in Pharmacotherapeutic Audit Meetings (PTAM). At PTAM meetings agreements are made to improve the pharmacotherapeutic care provided. A PTAM-group generally consists of 2 to 6 pharmacists from 2 to 3 pharmacies and 6 to 10 general practitioners. During this study three PTAM sessions are organized. The first to discuss the intervention. The second to make the agreements and the third PTAM sessions are used to evaluate, the procedure.

#### Control Group

Patients of control pharmacists will receive usual care according to the Dutch Pharmacy Standard (Table 1). Furthermore, patients are visited once by a pharmacy technician and asked about possible drug related problems. These problems will be registered for scientific use only.

**Table 1 T1:** Usual care, according to the Dutch Pharmacy Standard

1	Preceding the release check, prescriptions are routinely checked for drug interactions and contra-indications by the PAIS.
2	Discharge medication is delivered at the patients' home or is picked up by the patient or carer in the pharmacy.
3	Drugs are routinely delivered with a drug information leaflet but patients often are also handed supplementary personalized PAIS-generated information letters on newly prescribed drugs.
4	When the discharge medication is collected from the pharmacy, the patient or carer is also provided with additional oral information about newly prescribed drugs. This includes an explanation of the drugs' actions, their use and of possible side effects.

First edition of 1996. The current (2nd) edition was introduced in 2006 (KNMP, The Hague).

